# Peer-delivered systems-integrated suicide prevention for women in Pakistan: a protocol for hybrid type II pilot cluster randomized controlled trial

**DOI:** 10.1186/s40814-026-01841-7

**Published:** 2026-06-13

**Keywords:** Suicide prevention, Maternal health, Implementation science, LMIC, Peer interventions, Health systems, Pilot randomized controlled trial, Pakistan

## Abstract

**Background:**

South Asia has the highest rates of suicide fatalities among women globally. Existing suicide prevention interventions are largely based on Western-informed risk reduction programs and theories. This pilot trial aims to test the acceptability and feasibility of a co-designed suicide prevention program for peri-rural Pakistani women called the Khushal Pur-Umeed Zindagi (KPZ, خوشحال پُرامید زندگی پروگرام), compared to enhanced usual care (EUC). The study seeks to innovate suicide prevention by grounding interventions in decolonized frameworks, leveraging peer mothers, and developing robust health system integration strategies.

**Methods:**

We will conduct a two-arm, mixed-methods, hybrid type 2, stratified pilot cluster randomized controlled trial in peri-rural areas of the Islamabad Capital Territory (ICT). KPZ is a decolonized, culturally salient brief intervention combining narrative-based safety planning and contact follow-up, delivered by peer mothers over 6 months. EUC entails the WHO *Mental Health Gap Action Programme* (mhGAP) suicide prevention module, along with referral support delivered through Primary Health Care (PHC) by Medical Officers (*n* = 2) and Lady Health Worker teams (*n* = 11). KPZ is integrated into the PHC system and is implemented through close collaboration between peer mothers (delivery agents) and the government-employed LHWs. A cohort of peer mothers (*n* = 11), identified from the same communities as participants, will be trained and supervised for the study duration. We will enroll 50 women aged 18–45 with a child under 3 years who report suicidal ideation and will conduct follow-ups at 3- and 6-months post-recruitment. Qualitative interviews with trial participants and periodic reflections from peer mothers will be conducted iteratively over 6 months. A mixed-methods approach will be used to assess both clinical and implementation outcomes. Primary clinical outcomes include suicidal ideation severity and suicidal behaviors. Implementation outcomes include feasibility, acceptability, fidelity, appropriateness, and peer mothers’ competence. Secondary outcomes assess additional clinical domains (depression, anxiety) and culturally relevant constructs (moral injury, cultural suicide cognitions).

**Discussion:**

This pilot trial will provide evidence on the feasibility and acceptability of integrating a decolonized, peer-delivered suicide prevention program for women into the existing Pakistani health system. The findings have the potential for large-scale public health impact by improving the availability, accessibility, and quality of culturally appropriate suicide prevention interventions in resource-constrained and complex environments. Results will inform a larger definitive trial of a community-initiated suicide prevention program in Pakistan.

**Trial registration:**

NCT06208293

**Supplementary Information:**

The online version contains supplementary material available at 10.1186/s40814-026-01841-7.

## Background

### Burden of suicide in low- and middle-income countries

Suicide remains a major and preventable cause of death worldwide, with an estimated 727,000 deaths and more than 20 million suicide attempts occurring each year [1]. The burden of suicide is borne disproportionately by low- and middle-income countries (LMICs), which accounted for nearly 73% of all global suicide deaths in 2021 [1]. Despite this inequitable distribution, the evidence base for suicide prevention interventions remains heavily skewed toward high-income settings, with relatively few interventions developed, adapted, or rigorously evaluated in LMIC contexts.

Preventing suicide is recognized as a global public health priority and is explicitly embedded within the United Nations Sustainable Development Goals (SDGs) [2]. Suicide mortality rate is captured under Indicator 3.4.2 of SDG 3 (Good Health and Well-being) [2], underscoring international commitments to reduce premature mortality from non-communicable conditions, including suicide. However, progress toward this target has been uneven, particularly in resource-constrained settings where structural inequities, limited mental health infrastructure, and sociocultural barriers continue to constrain effective prevention efforts [3, 4]. This study directly aligns with SDG 3 by addressing the critical gap in contextually grounded, scalable suicide-prevention strategies in LMICs, with the aim of contributing to reductions in suicide-related mortality among populations at heightened risk.

### Burden of maternal suicide in LMICs and Pakistan

Maternal suicide is a critical yet under-recognized contributor to maternal mortality in LMICs. Estimates suggest that up to 20% of maternal deaths in LMIC settings are attributable to suicide, and that as many as 27% of women experience suicidal ideation during the perinatal period [5, 6]. Despite this significant burden, robust surveillance data on maternal suicide remain limited in many resource-constrained LMIC contexts, constraining both accurate estimation and effective prevention planning.

Available evidence nonetheless points to important regional and gendered differences in suicide risk profiles. In high-income countries, suicide mortality rates are consistently higher among men than women, with an approximate male-to-female ratio of 5:3. In contrast, in South Asia this ratio is nearly equal, indicating that women in the region account for a substantially larger proportion of suicide deaths than is observed in high-income settings [7]. This pattern underscores the need for context-specific, gender-responsive suicide prevention strategies.

In Pakistan, the estimated suicide rate in 2019 was 8.9 deaths per 100,000 population [8]. Although suicide was decriminalized in Pakistan in 2022 [9], the extent to which this policy shift has translated into improved reporting, access to care, or changes in social attitudes remains largely unknown. Recent qualitative and mixed-methods research has begun to address these gaps by generating grounded theories that identify key psychosocial and structural targets for suicide prevention among women [10], as well as documenting the intergenerational consequences of maternal suicidality for child mental health and development [11].

Taken together, these findings highlight an urgent need for gender-sensitive, community-anchored, and systems-integrated approaches to suicide prevention that address both individual distress and the broader social and structural determinants shaping maternal suicidality in Pakistan and similar LMIC contexts.

### Suicide prevention interventions in LMICs and the need for task-shifted, decolonized, community-anchored, peer-led, and systems-integrated suicide prevention

To date, there are few community-based suicide prevention interventions for adults in LMICs, and even fewer that explicitly target women, despite women bearing a disproportionate burden of suicide attempts in South Asia. Most existing evidence from LMICs has focused either on clinical populations with recent histories of self-harm or on facility-based detection and referral, rather than on preventive, community-anchored approaches.

In South Asia, one of the most robust adult suicide prevention trials is the culturally adapted manual-assisted problem-solving intervention (C-MAP), which demonstrated feasibility and effectiveness in reducing suicidal ideation among adults with a recent history of self-harm [12]. While C-MAP represents an important advance in culturally responsive intervention development, it targeted individuals already engaged with clinical services following severe self-harm and required delivery by trained mental health professionals [12], limiting its scalability in settings with constrained specialist capacity. At the systems level, the World Health Organization’s (WHO) *Mental Health Gap Action Programme* (mhGAP) includes guidance on the identification and management of self-harm and suicide risk [2], yet implementation has largely relied on generalist clinicians and facility-based care, with limited attention to sustained, community-level prevention or gender-specific needs. mhGAP in Pakistan has not been evaluated for its impact on suicide prevention.

Task-shifting has emerged as a key strategy for reducing the burden of mental health conditions in low-resource contexts [3, 13, 14]. However, important gaps remain in understanding how best to adapt and deliver suicide prevention interventions across both low- and high-resource settings. Strengthening suicide prevention requires moving beyond reliance on clinical specialists and meaningfully involving non-specialist providers for timely detection and intervention.

Although evidence-based practices (EBPs) for suicide prevention exist, little is known about their implementation in contexts with limited access to mental health care. To address this, the WHO has recommended non-specialist, low-cost EBPs, such as the Brief Intervention and Contact (BIC), for suicide prevention in LMICs [15]. BIC has been tested with clinicians in several LMICs, including one hospital in Pakistan, and more recently was combined with safety planning, an approach involving personalized coping strategies and support contacts during suicidal crises, delivered by peers in India [12, 15–17].

Building on these efforts, Pakistan has already demonstrated the potential of task-shifting models. Lay peers (i.e., non-specialists) have been successfully engaged to deliver interventions for maternal depression and related mental health concerns [13, 14, 18, 19]. Importantly, stigma remains one of the most significant barriers to suicide disclosure, detection, and care in South Asia [20–22]. Families often conceal suicidal behavior due to fears of social judgment, loss of honor, and religious condemnation, which contributes to severe under-reporting and delayed help-seeking [23, 24].

Saeed and colleagues’ [10] grounded theory study on maternal suicidality in Pakistan further illuminates the psychosocial mechanisms that interventions should target. Women’s suicidal thoughts and behaviors were largely shaped by social isolation and neglect within the *susraal* (in-laws’ home), psychological distress related to the demands of motherhood, unresolved grief, and diminished *sabr* (patience). Protective factors included religious faith and a sense of duty toward children. These findings highlight the need for interventions that can reduce isolation, normalize conversations about distress, address stigma, and provide culturally sensitive emotional support mechanisms that peer-delivered programs are uniquely positioned to address.

Peers are therefore not only feasible and acceptable delivery agents, particularly among women, but also ideally suited to intervene on the culturally and contextually specific drivers of maternal suicidality identified in this study. By leveraging trust, proximity, and shared cultural experience, peers can help bridge Pakistan’s substantial mental health treatment gap while targeting the most salient mechanisms of risk and protection [24, 25]. Accordingly, this research targets peers to implement a culturally informed suicide prevention intervention.

### Pilot trial rationale

This study seeks to move beyond traditional Western paradigms and center locally grounded, culturally responsive approaches for suicide prevention. Our team sought to co-design a decolonized and community-anchored suicide prevention intervention for women by foregrounding epistemological diversity and leveraging scalable, task-shifted implementation strategies suitable for resource-constrained settings [26]. In Pakistan, community health workers and non-clinical Peers have been successfully engaged in the delivery of evidence-based interventions for maternal depression in close partnership with the health system [14, 27, 28]. Building on this strong implementation foundation, we co-developed a community-based, peer-delivered suicide prevention programme tailored to the sociocultural context of Pakistan through extensive formative research and sustained engagement with individuals and families with lived experience of suicidality [10]. Importantly, this work aligns with global public health priorities articulated in the WHO’s *LIVE LIFE* Initiative, a comprehensive framework guiding countries in scaling up evidence-based suicide prevention strategies [1]. Community-based, peer-delivered interventions directly advance the two focal domains of early identification and support for everyone affected by suicide. Collectively, our approach contributes to global efforts to achieve SDG 3 of reducing suicide mortality by one-third by 2030 [2].

To date, the Khushal Pur-Umeed Zindagi (KPZ, خوشحال پُرامید زندگی پروگرام) program has not been evaluated for its acceptability, feasibility, or implementation potential within community settings in Pakistan. We therefore undertake a pilot randomized controlled trial to assess the acceptability and feasibility of implementing KPZ among married women in the maternal period, defined as those who are currently pregnant or have a child under 3 years of age. This manuscript describes the protocol for the pilot trial of the KPZ programme in peri-rural Pakistan. The specific objectives of the study are outlined below.

### Objectives of the study

To evaluate the feasibility of the peer-delivered KPZ intervention for reducing suicidal ideation, behaviours, and attempts among adult married women in the peri-rural areas of Islamabad capital Territory (ICT), Pakistan.To evaluate the preliminary effectiveness of the peer-delivered KPZ intervention in reducing suicidality and improving mental well-being among adult married women, compared with Enhanced Usual Care (EUC), at 3- and 6-months post-recruitment in Pakistan.To assess the acceptability and appropriateness of the KPZ intervention and its implementation among peer mothers and participants.To evaluate the appropriateness of KPZ and trial safety procedures, from the perspectives of married women, peer mothers, trainers, and primary health care providers.To assess treatment adherence among adult married women receiving peer-delivered KPZ intervention sessions.To assess the preliminary fidelity of KPZ intervention implementation.

### Study design

The study is a mixed-methods pilot hybrid type-II stratified cluster randomized controlled trial (cRCT), with six Village Clusters (VCs) allocated in a 1:1 ratio either to the intervention or EUC arm across two UCs (Shah Allah Ditta and Sihala). All study elements were designed alongside a Community Advisory Board (CAB) comprising five women with lived experience of suicidal thoughts or behavior and two LHWs from the study sites. The CAB provided ongoing feedback on all study materials, including recruitment procedures, intervention content, assessment tools, and implementation strategies, ensuring cultural relevance, acceptability, and feasibility. The CAB initially met quarterly during the co-design phase and then annually throughout the study to guide research operations. Recruitment of women of reproductive age is planned to span 1.5 years, with endline follow-ups of all participants 6 months post-recruitment beginning in May 2024.

Mixed-methods include quantitative measures and multiple qualitative methods, including longitudinal periodic reflections, in-depth interviews, focus group discussions, and systematic meeting debriefs to assess implementation outcomes and mechanisms. Longitudinal periodic reflections involve recurring discussions with implementing agents, namely peer mothers, to capture their evolving experiences, challenges, and adaptations over the course of intervention delivery. In-depth interviews with trial mothers, peer mothers, and health system clinicians elicit detailed insights into the feasibility, acceptability, and perceived mechanisms of change, as well as familial, social, and political factors influencing engagement and implementation. Systematic meeting debriefs provide documentation of emerging issues, solutions, and contextual factors that may affect implementation fidelity, reach, and sustainability of the intervention. Together, these qualitative methods allow for a comprehensive understanding of both participant and implementer experiences, inform iterative improvements, and contextualize quantitative outcome measures within the lived realities of the study setting.

### Randomization

The unit of randomization will be the VC. Each VC comprises 2–3 adjoining LHW catchment areas, with a total population of approximately 2400–3600 individuals. Randomizing at the VC level minimizes the risk of contamination between study arms. Six eligible VCs, across two UCs, will be randomized to the intervention or control arms using a 1:1 allocation ratio, with stratification at the UC level. Randomization will occur prior to participant identification and recruitment. Research teams responsible for participant identification, consent, and recruitment will remain blinded to VC allocation to minimize post-randomization recruitment bias.

Stratification at the UC level enhances study precision and statistical power by reducing variability between intervention and control VCs. It also helps prevent imbalances across arms that could result from UC-level factors, such as socioeconomic development, which may influence study outcomes. The randomization process and overall study design are illustrated in a CONSORT flow diagram (Fig. 1), prepared in accordance with the CONSORT extension for pilot cluster randomised trials [29]. VCs will be randomized through a computer-generated program by an individual at Yale University not involved in the day-to-day activities of the trial.

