#### Sampling procedures

The trial aims to recruit a total of 50 participants at risk of suicide and allocated into two equal groups: an intervention arm (*n* = 25) and an EUC arm (*n* = 25) based on their cluster randomization. This sample size is consistent with recommended guidelines for pilot randomized-controlled trials [30] and is sufficient for the primary goal of estimating key feasibility parameters, including recruitment rates, retention, and preliminary effect sizes, to inform the design of a future definitive trial, rather than for testing statistical significance. Participants will be identified by screening for suicidal ideation (in partnership with the local government health system) across six VCs. Based on extant literature and preliminary formative data, which estimate a 5–8% prevalence rate, we will screen approximately 800 women to ensure adequate recruitment across this range. The target analytic sample for all subsequent 3- and 6-month follow-up assessments will remain 50 participants, with robust retention strategies employed to minimize attrition. We will also aim to recruit 12 peer mothers to be trained as delivery agents for the KPZ intervention.

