Primary and secondary clinical outcomes will be analyzed using mixed-effects models to account for clustering within villages and repeated measures within participants. Continuous outcomes will be analysed using linear mixed-effect models, and binary outcomes using generalized linear mixed-effects models with a logit link, each including fixed effects for study arm, time, and their interaction, and random intercepts for village and participant. Missing data will be handled using these linear mixed-effects models, which account for missingness under the missing at random (MAR) assumption by utilizing all available data points for each participant. Analyses are exploratory and will emphasize effect size estimation and 95% confidence intervals, rather than statistical significance, consistent with the pilot design. To ensure the coverage of confidence intervals is accurate, the Kenward-Roger degrees of freedom correction will be applied to all mixed-effects models. This method specifically corrects both the degrees of freedom and the standard errors to account for the uncertainty in variance component estimation that arises with few clusters, and is expected to produce wider, more conservative confidence intervals. Furthermore, if the model encounters a singular fit due to limited cluster-level information, Bootstrap confidence intervals (percentile method, 1000 iterations) will be utilized as a robust sensitivity analysis, as this does not rely on variance component estimation.

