### Power calculation

As outlined by biostatisticians Thabane and Leon, pilot trials are not powered for statistical analysis [46, 47], but data will be monitored regularly. This study is not designed as a definitive, fully powered cRCT but rather as a feasibility/pilot trial intended to inform the power and sample size calculations for a future definitive cRCT and to estimate the Intra-cluster Correlation Coefficient (ICC) for our primary outcomes of interest. Our randomization strategy involves stratification at the UC level, with village clusters randomized 1:1 within each Union Council, to improve the precision of our estimates and provide critical data for the design of the future trial.

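### The analysis model omits Union Council, the stratification factor, and leaves the baseline arm difference free; this inflates the ICC and costs efficiency in the BSSI effect

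*Protocol article*

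**What the plan says.** Randomization is by village cluster (VC): "Six eligible VCs, across two UCs, will be randomized to the intervention or control arms using a 1:1 allocation ratio". The allocation is stratified by UC. The same section credits the stratification with a gain: "Stratification at the UC level enhances study precision and statistical power by reducing variability between intervention and control VCs". The Power calculation section repeats the precision argument ("village clusters randomized 1:1 within each Union Council, to improve the precision of our estimates") and makes estimation of the ICC for the primary outcomes a purpose of the pilot.

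Under Quantitative analysis, primary and secondary clinical outcomes go into mixed models that allow for village clustering and repeated measures. The terms are listed as "each including fixed effects for study arm, time, and their interaction, and random intercepts for village and participant". UC is not among the terms, and no baseline covariate is listed. The section adds the Kenward-Roger correction and places the weight on effect sizes and 95% confidence intervals. It does not say whether the reported effect is the arm-by-time interaction or the arm difference at 6 months.

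Table 1 and the section on primary clinical outcomes give BSSI and C-SSRS two time points only, baseline and 6 months.

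**The concern.** A stratified design lowers the true variance of the arm difference. The reported standard error shows that gain only if the stratum is in the model. Otherwise the difference between the two UCs is counted as random variation between villages. Here the same village variance also supplies the ICC for planning the definitive trial, so an inflated value would carry over into that trial's sample size.

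Baseline handling is a separate matter. With two visits and an unconstrained baseline arm difference, the interaction subtracts the whole baseline difference instead of the regression-weighted part. In a pilot whose main clinical output is an estimate with an interval, that efficiency counts.

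The article lists the model terms explicitly, along with the degrees-of-freedom method and a bootstrap fallback. The omission is therefore in the stated model and is not a detail left open for an analysis plan.

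**Working it through.** The protocol gives no SD, ICC, correlation or precision figure, so there is none to reproduce. **From the document:** 6 VCs, 2 UCs, 25 women per arm, hence 50/6 = 8.33 per VC. **Assumed:** outcome SD 1 within UC; ICC 0.05; UC difference D from 0 to 1 SD; baseline-to-6-month correlation r from 0.3 to 0.7; VC split 4+2, or 3+3 where named.

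**1. Baseline.** Per-woman variance is 2(1 − r) for a change score and 1 − r² for ANCOVA. The ratio is 2/(1 + r), and the interval-width ratio is its square root.

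| r | change score | ANCOVA | variance ratio | width ratio |
|---|---|---|---|---|
| 0.3 | 1.40 | 0.91 | 1.54 | 1.24 |
| 0.5 | 1.00 | 0.75 | 1.33 | 1.15 |
| 0.7 | 0.60 | 0.51 | 1.18 | 1.08 |

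These ratios compare like with like: participant-level variation and the same critical value on both sides.

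**2. ICC.** With arm in the model and UC left out, each arm of three VCs has two from one UC and one from the other. The within-arm sum of squares of the UC indicator is 2/3 per arm, or 4/3 in total, on 6 − 2 = 4 degrees of freedom. The variance added to the village component is D² × (4/3)/4 = D²/3. A 3+3 split allocated 2:1 and 1:2 gives the same figure.

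- D = 0.5: 0.25/3 = 0.083; ICC = (0.05 + 0.083)/(1 + 0.083) = 0.12.
- D = 0.8: 0.64/3 = 0.213; ICC = (0.05 + 0.213)/(1 + 0.213) = 0.22.

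With six VCs the ICC is imprecise in any case. Around an estimate of 0.05, the F-based 95% interval (4 and 44 degrees of freedom, 8.33 per VC) runs from −0.07 to 0.57.

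**3. Arm difference at 6 months.** Cluster means were simulated for a 4+2 split with ICC 0.05. The table gives the mean 95% half-width in SD.

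| D | without UC | with UC | ratio | coverage without UC |
|---|---|---|---|---|
| 0 | 0.86 | 0.97 | 0.89 | 95.0% |
| 0.25 | 0.92 | 0.97 | 0.94 | 96.0% |
| 0.5 | 1.07 | 0.97 | 1.10 | 97.6% |
| 0.8 | 1.33 | 0.97 | 1.38 | 99.2% |
| 1.0 | 1.54 | 0.97 | 1.59 | 99.7% |

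At D = 0.8 the true standard error is 0.33, while the model without UC reports about 0.50. Break-even is near D = 0.35. Below it, adjustment widens the interval, because VC-level degrees of freedom fall from 4 to 3 and the critical value rises from 2.78 to 3.18 (ratio 1.15).

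**4. Arm-by-time contrast.** In 40 simulated data sets fitted with the protocol's terms, adding a UC main effect changed the interaction estimate by nothing beyond rounding. The mean standard error was 0.279 without UC and 0.280 with it. A constant UC difference cancels from this contrast.

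**5. VC split.** The Power calculation section has "with village clusters randomized 1:1 within each Union Council". With three VCs per arm, exact balance inside both UCs needs an even number in each: 2+4 works, 3+3 does not. The text does not give the split.

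**The case against.** The strongest reply is that little is lost. The trial is an exploratory, unpowered pilot. Stratification still balances the arms and lowers the true variance whatever the model contains. Leaving UC out errs on the safe side. With six clusters, spending one of four degrees of freedom on UC can widen the interval, and the Study setting section describes two UCs with similar economies and facility staffing. All of this stands. It limits the weight of the point but does not answer the ICC problem, which arises whichever contrast is reported.

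Four stronger readings are tempting, and the documents do not support them.

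- **The precision from stratification is lost outright.** This depends on the contrast and on the size of the UC difference. It does not hold for the linear arm-by-time effect, nor for a 6-month difference when the UCs are similar.
- **Baseline is ignored.** It is not: it enters as one of the two repeated outcome values. The weakness is the unconstrained contrast, which has nothing to do with stratification.
- **Both interval losses fall on one estimate.** They do not. The change-score loss belongs to arm-by-time, and the UC loss to the 6-month level difference.
- **The split is 3+3, so arm and UC are partly confounded.** Nothing says 3+3, and the flow diagram, which may show the split, is not in the text at hand. Only if it were 3+3 would a third of a UC difference (2/3 − 1/3) enter an unadjusted 6-month contrast.

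Constraining baseline means to be equal would also be open to challenge, because VCs are randomized before women are identified. ANCOVA needs no such constraint.

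**Conclusion.** The point holds in limited form. The stated model leaves out the factor to which the protocol attributes precision, and it uses baseline less efficiently than it could. Three consequences remain:

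- the BSSI change-score contrast is about 8% to 24% wider than ANCOVA at assumed r of 0.7 to 0.3, like for like;
- an assumed ICC of 0.05 is inflated to about 0.12 or 0.22 at UC differences of 0.5 or 0.8 SD;
- intervals for a 6-month arm difference are about 1.1 or 1.4 times too wide at those same differences (4+2 split, ICC 0.05).

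The third is conservative. The most consequential is the ICC, because it is carried into the next trial. Every size rests on assumed correlations, ICC and UC differences, since the protocol gives none. The results are for the linear model and do not transfer exactly to the logistic model for C-SSRS.

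**What to change.** Change the wording under Quantitative analysis before outcome data are analysed by arm:

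- Name the arm difference at 6 months as the effect to be reported.
- For BSSI, model the 6-month value with fixed effects for arm, baseline value and UC, plus a VC random intercept.
- Report the ICC within UC with its interval, and pass it to the definitive trial as a range, not as a single planning value.
- State the number of VCs per UC and confirm that it permits the stated 1:1 allocation within each UC; if it does not, correct that statement.
- Show the result without UC as a sensitivity analysis.

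No new data are needed. The price is one of four VC-level degrees of freedom (critical value 2.78 to 3.18), so the interval widens if the UCs differ by less than about 0.35 SD (4+2 split, ICC 0.05). The ANCOVA effect is also a comparison between villages and is judged on those few degrees of freedom. In the protocol's model the village intercept cancels from arm-by-time, so that contrast is not charged for them. The printed interval may therefore not be narrower than the current model's, even though the use of baseline is more efficient.
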